**Table 1. Intervention groups and regimens**

| Study group and child age | Contents of intervention products |                            |
|---------------------------|-----------------------------------|----------------------------|
|                           | LNS                               | Zinc or placebo supplement |
| Age 9-17 mo.       |                                   |                            |
| LNS-Zn0                   | 0 mg zinc in 20 g LNS/day         | Placebo daily              |
| LNS-Zn5                   | 5 mg zinc in 20 g LNS/day         | Placebo daily              |
| LNS-Zn10                  | 10 mg zinc in 20 g LNS/day        | Placebo daily              |
| Suppl-Zn5                 | 0 mg zinc in 20 g LNS/day         | 5 mg zinc supplement daily |
| ST-DI                     | Standard care                     | Standard care              |
| Age 18-27 mo.      |                                   |                            |
| LNS-Zn0                   | Standard care                     | Standard care              |
| LNS-Zn5                   | Standard care                     | Standard care              |
| LNS-Zn10                  | Standard care                     | Standard care              |
| Suppl-Zn5                 | Standard care                     | Standard care              |
| ST-DI                     | 10 mg zinc in 20 g LNS/day        | No supplement              |
| Age 28-42 mo.      |                                   |                            |
| LNS-Zn0                   | Standard care                     | Standard care              |
| LNS-Zn5                   | Standard care                     | Standard care              |
| LNS-Zn10                  | Standard care                     | Standard care              |
| Suppl-Zn5                 | Standard care                     | Standard care              |
| ST-DI                     | Standard care                     | Standard care              |

The LNS will be delivered in plastic pots containing 140 g (sufficient for one week) or sachets containing 20 g (the dose for one day) and labeled individually with one of 8 color codes (two colors per treatment group) to avoid the possibility of any mix-ups during delivery to the household. The child's caregivers will be provided with a measuring spoon and advised to feed the day's allotment (20 g = 2 spoonfuls) in two servings at meal times (1 spoonful per each of two meals). In particular, the caregiver will be requested to add 1 spoonful of LNS to ~2 tablespoons of cereal porridge or other complementary food and then to continue feeding any desired additional amount of the food. This is to maximize the likelihood that all of the prescribed LNS dose will be served each meal.

All mothers will be encouraged to continue breastfeeding on demand.

The LNS will be produced and packed by Nutriset (Malaunay, France). Raw ingredients include peanut paste, dried skimmed milk, maltodextrin, sugar, vegetable oil, and a mineral and vitamin mix. The products are packed in opaque, plastic containers, each containing 140 g of the supplement or foil sachets containing 20 g of the LNS. LNS containers will be stored in the Bama field office at a temperature between 20°C and 40°C. At these temperatures, the nutritional quality is guaranteed for 12 months. Because of low water activity, the products are resistant to microbial contamination. The specific nutrient content of each is summarized in Table 2.

**Table 2: Serving size and nutrient composition of the food supplements for the trial**

| Nutrient                    | LNS-Zn0 | LNS-Zn5 | LNS-Zn10 |
|------------------------------------|----------------|----------------|-----------------|
| Ration (g/day)                     | 20             | 20             | 20              |
| Total energy (kcal)                | 124            | 124            | 124             |
| Protein (g)                        | 2.6            | 2.6            | 2.6             |
| Fat (g)                            | 9.6            | 9.6            | 9.6             |
| Linoleic acid (g)                  | 4.5            | 4.5            | 4.5             |
| $\alpha$ -Linolenic acid (g)       | 0.58           | 0.58           | 0.58            |
| Vitamin A ( $\mu$ g RE)            | 400            | 400            | 400             |
| Vitamin C (mg)                     | 30             | 30             | 30              |
| Vitamin B 1 (mg)        | 0.3            | 0.3            | 0.3             |
| Vitamin B 2 (mg)        | 0.4            | 0.4            | 0.4             |
| Niacin (mg)                        | 4              | 4              | 4               |
| Folic acid ( $\mu$ g)              | 80             | 80             | 80              |
| Pantothenic acid (mg)              | 1.8            | 1.8            | 1.8             |
| Vitamin B 6 (mg)        | 0.3            | 0.3            | 0.3             |
| Vitamin B 12 ( $\mu$ g) | 0.5            | 0.5            | 0.5             |
| Vitamin D (IU)                     | 200            | 200            | 200             |
| Vitamin E (mg)                     | 6              | 6              | 6               |
| Vitamin K ( $\mu$ g)               | 30             | 30             | 30              |
| Iron (mg)              | 6              | 6              | 6               |
| Zinc (mg)                          | 0.3            | 5.3            | 10.3            |
| Cu (mg)                            | 0.2            | 0.2            | 0.2             |
| Calcium (mg)                       | 280            | 280            | 280             |
| Phosphorus (mg)                    | 190            | 190            | 190             |
| Potassium (mg)                     | 200            | 200            | 200             |
| Magnesium (mg)                     | 40             | 40             | 40              |
| Selenium ( $\mu$ g)                | 20             | 20             | 20              |
| Iodine ( $\mu$ g)                  | 90             | 90             | 90              |
| Manganese (mg)                     | 1.2            | 1.2            | 1.2             |
| Phytate (mg)                       | n/a*           | n/a*           | n/a*            |

\* n/a: Information not available.

Target iron content has been reduced from 9 mg in Nutributter to 6 mg, to reduce any potential risk associated with iron intake in malarial areas. As the daily ration will be divided into at least 2 meals during the day, the amount of iron consumed at any single meal should not exceed 3 mg. This falls within the amount of iron that a fortified processed complementary food would provide at a given meal, which is considered acceptable by the World Health Organization/ United Nations Children's Fund (WHO, 2007)).

Zinc supplements will be provided as water-dispersible tablets produced by Nutriset (Malaunay, France) containing 5 mg of zinc per day or an identical product without zinc. The caregivers will be advised to provide the supplements once daily, either between meals or with breast milk, but not with other foods. The supplements will also be labeled individually with one of 8 color codes (the same colors per treatment group as for LNS) to avoid the possibility of any mix-ups during delivery to the household. Samples of the LNS and zinc supplements/placebos will be culled systematically for analysis of zinc content in an independent laboratory.

LNS supplementation will continue for 9 months, starting after baseline screening at nine (9.0 – 9.9) months and ending after 9 months when the participants are 18 (18.0 – 18.9) months old. For the delayed intervention group, LNS containing 10 mg of zinc per 20 g will be given from 18 to 27 months of age.

#### Other treatments provided to study participants

##### *Recommendations on infant feeding*

All groups, including the delayed intervention group, will receive simple messages on infant feeding from the study personnel at the time of baseline and final screening (age 9 and 18 months). The messages will include continued breast feeding, and in the intervention communities, instructions on how to feed LNS and the supplements.

##### *Health care*

The study participants will be advised to attend health centers according to the same routine schedule as all other Burkinabe infants and receive the usual services provided through the national health system. Participants with documented peripheral blood malaria parasitemia at any point of the trial will be treated with nationally recommended antimalarial drugs, currently a combination of artesunate and amodiaquine. Children with diarrhea will be treated with oral rehydration solution (ORS) packets and advised to continue feeding. Children with signs of dehydration, dysentery, or persistent diarrhea (>14 d) will be referred to the health center. The children presenting with symptoms of malaria or diarrhea will not be removed from the study. They will continue to receive the daily LNS and zinc/placebo supplement, in addition to whatever treatment is provided by their physician.

Participants with documented severe anemia (hemoglobin < 50 g/L) at any point of the trial will be referred for blood transfusion at national health facilities and will be excluded from the study at baseline. Participants with moderate anemia (hemoglobin between 50 and 79 g/L) will be treated according the national policy. Namely, they will receive iron supplementation (3-6 mg iron/kg/d for at least 30 days) and an anthelmintic treatment (Mebendazole). Participants requiring treatment at any timepoint during the study will remain in the study during and after the additional iron and anthelmintic treatment and will continue to receive LNS and zinc/placebo supplements, but will be specifically identified in the analyses. All other medical conditions will be treated by the Burkina Faso's health system, according to the standard national guidelines.

#### Surveillance during intervention and post-intervention data collection

##### a. Intervention groups

In the intervention groups, the families will receive the respective supplements at weekly intervals and the participants will undergo regular surveillance as described above. The scheduled data collection is summarized below in Table 3.

b. Delayed-intervention group

Children in the delayed intervention communities will be screened at baseline and at 18 months of age only (Table 4). During the 9-month supplementation period, the children in the delayed intervention group will not be visited.

**Table 3. Summary of data collection in relation to time of enrollment into the study - Intervention groups (LNS-Zn0, LNS-Zn5, LNS-Zn10, Suppl-Zn5)**

| Child age (months)                                                                                                                                                            | 09 | 10 | 11 | 12 | 13 | 14 | 15 | 16 | 17 | 18 | 19 | 20 | 21 | 22 | 23 | 24 | 25 | 26 | 27 | 28 | 30 | 36 | 42 |
|-------------------------------------------------------------------------------------------------------------------------------------------------------------------------------|----|----|----|----|----|----|----|----|----|----|----|----|----|----|----|----|----|----|----|----|----|----|----|
| Food supplement delivery (weekly)                                                                                                                                             | x  | x  | x  | x  | x  | x  | x  | x  | x  | x  |    |    |    |    |    |    |    |    |    |    |    |    |    |
| Morbidity and adverse events (weekly)                                                                                                                                         | x  | x  | x  | x  | x  | x  | x  | x  | x  | x  |    |    |    |    |    |    |    |    |    |    |    |    |    |
| Anthropometry                                                                                                                                                                 | x  |    |    | x  |    |    | x  |    |    | x  |    |    |    |    |    |    |    |    |    |    |    |    |    |
| Hemoglobin                                                                                                                                                                    | x  |    |    |    |    |    |    |    |    | x  |    |    |    |    |    |    |    |    |    |    |    |    |    |
| ZPP (capillary)                                                                                                                                                               | x  |    |    |    |    |    |    |    |    |    |    |    |    |    |    |    |    |    |    |    |    |    |    |
| Malaria (capillary and venous for biochemical subgroup)                                                                                                                       | x  |    |    |    |    |    |    |    |    | x  |    |    |    |    |    |    |    |    |    |    |    |    |    |
| Biochemistry (venous and capillary ZPP, zinc, retinol, retinol-binding protein, plasma ferritin, transferrin receptor, CRP, AGP; thyroid hormones, thyroglobulin in subgroup) | x  |    |    |    |    |    |    |    |    | x  |    |    |    |    |    |    |    |    |    |    |    |    |    |
| Body composition (saliva in subgroup)                                                                                                                                         | x  |    |    |    |    |    |    |    |    | x  |    |    |    |    |    |    |    |    |    |    |    |    |    |
| Urinary iodine (subgroup)                                                                                                                                                     | x  |    |    |    |    |    |    |    |    | x  |    |    |    |    |    |    |    |    |    |    |    |    |    |
| Socio-economic status                                                                                                                                                         | x  |    |    |    |    |    | x  |    |    |    |    |    | x  |    |    |    |    |    | x  |    |    |    | x  |
| Full food frequency questionnaire                                                                                                                                             | x  |    |    |    |    |    |    |    |    | x  |    |    |    |    |    |    |    |    |    |    |    |    |    |
| Household food security                                                                                                                                                       | x  |    |    |    |    |    | x  |    |    |    |    |    |    |    |    |    |    |    |    |    |    |    |    |
| 12-hour observation care & feeding practices (subgroup)                                                                                                                       |    | x  |    |    |    |    |    | x  |    |    |    |    |    |    |    |    |    |    |    |    |    |    |    |
| Developmental milestones (reported) and breastfeeding questions                                                                                                               | x  | x  | x  | x  | x  | x  | x  | x  | x  | x  |    |    |    |    |    |    |    |    |    |    |    |    |    |
| Developmental milestones (observed) and zinc food questions                                                                                                                   | x  |    |    | x  |    |    | x  |    |    | x  |    |    |    |    |    |    |    |    |    |    |    |    |    |
| Full developmental assessment (subgroup)                                                                                                                                      |    |    |    |    |    |    |    |    |    | x  |    |    |    |    |    |    |    |    |    |    |    |    |    |
| Caregiver knowledge, attitudes, practices (KAP)                                                                                                                               |    |    |    |    |    |    | x  |    |    |    |    |    |    |    |    |    |    |    |    |    |    |    |    |

**Table 4. Summary of data collection in relation to time of enrollment into the study - Delayed intervention group (ST-DI)**

| Child age (months)                                                                                                                                                          | 09 | 10 | 11 | 12 | 13 | 14 | 15 | 16 | 17 | 18 | 19 | 20 | 21 | 22 | 23 | 24 | 25 | 26 | 27 | 28 | 30 | 36 | 42 |
|-----------------------------------------------------------------------------------------------------------------------------------------------------------------------------|----|----|----|----|----|----|----|----|----|----|----|----|----|----|----|----|----|----|----|----|----|----|----|
| Food supplement delivery (monthly)                                                                                                                                          |    |    |    |    |    |    |    |    |    | x  | x  | x  | x  | x  | x  | x  | x  | x  | x  |    |    |    |    |
| Morbidity                                                                                                                                                                   | x  |    |    |    |    |    |    |    |    |    |    |    |    |    |    |    |    |    |    |    |    |    |    |
| Anthropometry                                                                                                                                                               | x  |    |    |    |    |    |    |    |    | x  |    |    |    |    |    |    |    |    |    |    |    |    |    |
| Hemoglobin                                                                                                                                                                  | x  |    |    |    |    |    |    |    |    | x  |    |    |    |    |    |    |    |    |    |    |    |    |    |
| ZPP (capillary)                                                                                                                                                             | x  |    |    |    |    |    |    |    |    |    |    |    |    |    |    |    |    |    |    |    |    |    |    |
| Malaria (capillary and venous in biochemical subgroup)                                                                                                                      | x  |    |    |    |    |    |    |    |    |    |    |    |    |    |    |    |    |    |    |    |    |    |    |
| Biochemistry (venous and capillary ZPP, zinc, retinol, retinol-binding protein, plasma ferritin, transferrin receptor, CRP, AGP; thyroid hormones, thyroglobulin; subgroup) | x  |    |    |    |    |    |    |    |    | x  |    |    |    |    |    |    |    |    |    |    |    |    |    |
| Body composition (saliva and urine in subgroup)                                                                                                                             | x  |    |    |    |    |    |    |    |    | x  |    |    |    |    |    |    |    |    |    |    |    |    |    |
| Urinary iodine (subgroup)                                                                                                                                                   | x  |    |    |    |    |    |    |    |    | x  |    |    |    |    |    |    |    |    |    |    |    |    |    |
| Socio-economic status                                                                                                                                                       | x  |    |    |    |    |    |    |    |    | x  |    |    | x  |    |    |    |    |    | x  |    |    |    | x  |
| Food frequency questionnaire                                                                                                                                                | x  |    |    |    |    |    |    |    |    | x  |    |    |    |    |    |    |    |    |    |    |    |    |    |
| Household food security                                                                                                                                                     | x  |    |    |    |    |    |    |    |    |    |    |    |    |    |    |    |    |    |    |    |    |    |    |
| 12-hour observation care & feeding practices (subgroup)                                                                                                                     |    |    |    |    |    |    |    |    |    |    |    |    |    |    |    |    |    |    |    |    |    |    |    |

|                                                                 |   |  |  |  |  |  |   |  |  |  |   |  |  |  |  |  |  |  |  |  |  |  |  |  |  |
|-----------------------------------------------------------------|---|--|--|--|--|--|---|--|--|--|---|--|--|--|--|--|--|--|--|--|--|--|--|--|--|
| Developmental milestones (reported) and breastfeeding questions |   |  |  |  |  |  |   |  |  |  |   |  |  |  |  |  |  |  |  |  |  |  |  |  |  |
| Developmental milestones (observed) and zinc food questions     | x |  |  |  |  |  |   |  |  |  | x |  |  |  |  |  |  |  |  |  |  |  |  |  |  |
| Full developmental assessment (subgroup)                        |   |  |  |  |  |  |   |  |  |  | x |  |  |  |  |  |  |  |  |  |  |  |  |  |  |
| Caregiver knowledge, attitudes, practices (KAP)                 |   |  |  |  |  |  | x |  |  |  |   |  |  |  |  |  |  |  |  |  |  |  |  |  |  |

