### **Morbidity surveillance**

In the intervention communities, field surveillance workers will visit each home in their assigned villages on a weekly basis during the intervention period to assess morbidity from common infections. Diarrhea will be defined as the presence of four or more loose or liquid stools per 24 hours, as reported to field workers by caregivers. Temperature and two one-minute respiratory rates will be measured by field workers on the first week of the month and whenever fever is reported or respiratory distress is observed. Upper respiratory infection will be defined as the presence of cough and purulent nasal discharge, and lower respiratory infection by the presence of cough and age-specific increase in respiratory rate (>50/minute for infants <12 months of age and >40/minute for older children). New episodes of diarrhea and respiratory infections will be considered when at least 72 hours have elapsed since a previous episode has resolved. Malaria will be assessed by the Rapid Diagnosis Test (HRP2, histidine-rich protein 2) and both thick and thin blood smears.

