The screening at 9 and 18 months of age will be identical for intervention and non-intervention communities. However, the children in the delayed intervention group will not be visited during the 9-month supplementation period. Thus, the study team will not be available to provide any treatment services or referrals, and the families will use the same medical services that are ordinarily available. The local services consist of a system of health centers and district-level referral hospitals, which offer services according to the WHO program for the Integrated Management of Childhood Illnesses (IMCI). IMCI is a simple algorithm based on clinical symptoms and signs that allows relatively untrained village health workers to diagnose and provide treatment for common childhood illnesses (diarrhea, acute lower respiratory tract infection, malaria, acute malnutrition) and referral for complicated cases. Currently, treatment of uncomplicated diarrhea in the community consists of oral rehydration solution and dietary counseling for continued feeding. Children with dehydration, dysentery, or persistent diarrhea are referred to the nearest health center for more extensive evaluation and treatment, including intravenous therapy and antibiotics when indicated. The reason for including the delayed intervention communities is to help with the interpretation of the growth data in the intervention communities. Children in the delayed intervention group will receive LNS with 10 mg zinc from the age 18 to 27 months, as described in Table 1.

In an effort to keep the anthropometrists, phlebotomists and other fieldworkers unbiased in their data collection activities, the study staff will be informed that the children in the delayed intervention communities are measured for census purposes only and that they are not part of the intervention study.

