## Interventions

After completion of baseline assessments, the children in the intervention groups will begin receiving the respective masked, color-coded intervention products (LNS and placebo or zinc supplements) daily for 9 months. The supplements will be distributed weekly by a field worker who will also assess the disappearance rate of the LNS and the supplements by estimating how much remains (0%, 25%, 50%, 75%, 100%) in the children's homes at the end of each week. Empty packages and any unconsumed supplements from the previous week will be gathered as markers of adherence.

Approximately, 2440 infants from the intervention communities who meet set criteria will be randomly assigned to receive the following intervention from 9 to 18 months of age:

- 1) LNS without zinc, placebo supplement (LNS-Zn0): 0 mg zinc in 20 grams LNS per day and a daily placebo supplement between meals from age 9 to 18 months.
- 2) LNS with 5 mg zinc, placebo supplement (LNS-Zn5): 5 mg zinc in 20 grams LNS per day and a daily placebo supplement between meals from age 9 to 18 months.
- 3) LNS with 10 mg zinc, placebo supplement (LNS-Zn10): 10 mg zinc in 20 grams LNS per day and a daily placebo supplement between meals from age 9 to 18 months.
- 4) LNS without zinc, 5 mg zinc supplement (Suppl-Zn5): 0 mg zinc in 20 grams LNS per day and a 5 mg zinc supplement between meals from age 9 to 18 months.

In addition, approximately 810 infants from the delayed intervention communities who meet set criteria will be assigned to the following group:

- 5) Standard treatment with delayed LNS intervention (ST-DI): Standard care from age 9 to 18 months; LNS containing 10 mg zinc per 20 grams LNS, delayed until age 18 to 27 months.

This information is summarized below in Table 1.

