### Nature, frequency and duration of tests

In all children, capillary blood samples will be obtained by finger stick upon enrollment (9 months of age) and at 18 months of age to measure hemoglobin and malaria parasites count. At 9 months, the finger stick will also be used to assess ZPP and malaria antigen. In the biochemistry subgroup, capillary ZPP will also be done at 18 months.

Biochemical indicators of micronutrient status will be assessed in a randomly selected sub-set of children (n=626). For these subjects, caregivers will bring their children to the clinic for the baseline and final specimen collections. Venous blood samples (5 ml whole blood) will be obtained from subjects at the baseline and final clinic visits. The samples will be drawn in the morning at the local community health center. When the child is ill or has had diarrhea or fever during the past two days of a scheduled baseline collection of blood, urine and saliva, the sample collection will be postponed until

the symptoms resolve. Final collection of blood, urine, and saliva will be postponed if the child has a fever  $>38.5^{\circ}\text{C}$  or is acutely ill. In the case of the final biochemical sample, supplementation will be continued until the sample is obtained.

In the intervention groups, the length, weight, right mid-upper arm circumference and head circumference will be measured for all children at the baseline, 12, 15 and 18 months of age during the intervention. The same anthropometric measurements will be completed for children in the delayed intervention group at baseline and 18 months of age. We anticipate that clinic visits including blood sample collection and anthropometry will take approximately 4-5 hours to complete.

In the “biochemistry” subset of children, body composition will be assessed twice, at baseline and 18 months of age, at the health center. We anticipate that the body composition assessment will take approximately 4-5 hours.

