**RISKS:**

The risks involved in this study are minimal. Although nutritional status can be assessed by clinical examination, biochemical assessment was selected because it permits assessment of multiple micronutrients over the full range of adequate status to mild, moderate, or severe deficiency.

Blood draws can cause momentary pain and discomfort and can result in bruising, but rarely result in infection or other complaints. Blood draws will be performed by qualified health professionals. Two capillary blood samples will be collected from all subjects at ages 9 and 18 months. In a sub-set of subjects, two 5-ml venous blood samples will be collected when participants are 9 and 18 months old. The collected volume represents <1% of the child's total blood volume and is replaceable from the child's own blood production within a day; the total volume of blood collected (10 ml) is minimal and unlikely to result in any adverse effects.

The study poses risks of psychological harm to participants as a result of inadvertent lack of respect for cultural norms, which is likely to be unpleasant but temporary. The risk will be minimized by consulting with local community leaders prior to the start of the study, and obtaining their permission to recruit subjects in their villages. IRSS,B, established in 1997, has developed excellent rapport with local community leaders and residents. Additionally, the majority of the study team members are from Burkina Faso and have extensive field experience that will be shared during training.

There is a risk of accidental release of personal health information which may have important social or psychological consequences for the subject. This risk will be minimized by the confidentiality measures described below.

Plan for protecting subject privacy and confidentiality.

Subject data will be identified with unique identification numbers, and full names will not be attached to the data. All documentation regarding the participants, including the laboratory samples, source data and the Adverse Event Form will be identified with appropriate participant codes, both on paper and in computer files. The full names will only appear on informed consent forms and a separate coding list.

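### Table 4 leaves out the 18-month malaria test in the delayed group, against the protocol's own text, and the planned malaria-incidence comparison with that group cannot be made

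*Protocol*

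**What the plan says.** **Schedules.** Table 3, for the four intervention groups, has a row labelled "Malaria (capillary and venous for biochemical subgroup" marked at 9 and 18 months. The matching row of Table 4, for the delayed group, is labelled "Malaria (capillary and venous in biochemical subgroup" and is marked at 9 months only. The subsection on the delayed-intervention group says these children are screened at baseline and 18 months, and points to Table 4 for the content.

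**Text.** The section on nature, frequency and duration of tests opens by referring to all children. It has a finger stick done on enrollment and "at 18 months of age to measure hemoglobin and malaria parasites count". The screening and baseline section states: "The screening at 9 and 18 months of age will be identical for intervention and non-intervention communities". The risks section states: "Two capillary blood samples will be collected from all subjects at ages 9 and 18 months".

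**Follow-up between the two screens.** The morbidity section reads: "In the intervention communities, field surveillance workers will visit each home in their assigned villages on a weekly basis". For the other communities the screening section says that "the children in the delayed intervention group will not be visited during the 9-month supplementation period". The delayed group's regimen over this period is "Standard care from age 9 to 18 months", while all four other groups receive LNS.

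**Analysis.** The data entry and analysis section lists incidence of malaria among the primary outcomes. It plans two sets of contrasts for those outcomes: the zinc groups against LNS-Zn0, and all intervention groups against the delayed group.

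**The concern.** Table 4 is the document that tells a field team what to do at the delayed group's 18-month visit. Read alone, it calls for hemoglobin, anthropometry and the biochemical subgroup samples, but no malaria test. The text says otherwise. A team following the table would take the finger stick and not examine it for parasites, and a sample not examined at 18 months may not be recoverable.

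The 18-month test is the only malaria observation the delayed group can have after baseline, since no one visits these children in between. The protocol nevertheless lists malaria incidence among the outcomes to be compared with that group. At stake are whether any post-baseline malaria data exist for about a quarter of the trial, and whether the stated comparison is one the design can deliver.

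**Working it through.** No sample size or power figure is involved, so the check sets the places in the protocol side by side.

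**Step 1: is the empty cell real?** Each table has 23 age columns. The rows were split into cells and matched to those columns.

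| Row | Cells | Months marked |
|---|---|---|
| Table 3, hemoglobin | 23 | 9, 18 |
| Table 3, malaria | 23 | 9, 18 |
| Table 4, hemoglobin | 23 | 9, 18 |
| Table 4, biochemistry | 23 | 9, 18 |
| Table 4, malaria | 23 | 9 |

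Every row has the right number of cells, and the neighbouring rows carry their 18-month mark in the right column. The empty malaria cell is therefore not a column shift from text extraction.

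**Step 2: does the text call for the test in this group?** The tests section names parasite count at 18 months and applies it to all children, so it does. The risks section confirms that capillary blood is drawn from every child at both ages ("Two capillary blood samples will be collected from all subjects at ages 9 and 18 months"). The statement that screening is identical points the same way. Table 4 itself marks hemoglobin at 18 months, so even on the table's reading the finger stick takes place.

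**Step 3: how many children?** The subject selection section gives 610 per intervention group and about 810 in the delayed group: 4 × 610 = 2440, and 2440 + 810 = 3250, which reproduces the stated total. The delayed group is 810 / 3250 = 24.9% of the trial. Under Table 4, about 810 children have no malaria result after baseline, while about 2440 are scheduled to have one at 18 months.

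**Step 4: would restoring the mark rescue the planned comparison?** No. Incidence needs episodes counted over time at risk. In the intervention communities this comes from weekly visits with a rapid test when there is fever. In the delayed group nothing is recorded between 9 and 18 months. One parasite count at 18 months gives point prevalence. The incidence contrast with the delayed group is therefore unobtainable both with and without the mark.

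**Step 5: what would an 18-month prevalence contrast measure?** The safety monitoring section has intervention children tested at home visits when fever is found or reported, and treated under national guidelines if positive. The screening section says delayed-group families use ordinary services and that the study team offers no treatment or referral in that period. A difference in prevalence at 18 months would combine any effect of LNS with nine months of active case detection and treatment on one side only.

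**The case against.** The strongest reply is that Table 4 is headed as a summary, that the body text is consistent across three sections, and that a missing mark is most simply a clerical slip. On that reading the test is done and nothing is lost. This stands in part: the protocol does not settle on omitting the test, it gives two instructions. It does not dispose of the point, because the delayed-group subsection sends the reader to Table 4.

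A second reply is that malaria is not what the delayed group is for. The screening section gives interpretation of the growth data as its purpose, and the second hypothesis covers growth only. This stands and limits the damage. It does not remove the sentence in the analysis section that includes malaria incidence in the comparison.

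Some stronger readings are tempting but not supported:

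- *The trial will have no malaria result against its only unsupplemented group.* This holds only if the table overrides the text, which nothing in the protocol says.
- *Restoring the mark would give a clean LNS versus no-LNS malaria comparison, perhaps as a check on the reduced iron content.* Step 5 shows why it would not. The iron footnote to Table 2 explains the formulation and announces no such comparison.
- *The morbidity row of Table 4, also marked at 9 months only, has the same defect.* The Table 3 row covers weekly surveillance and adverse events. The protocol limits weekly surveillance to the intervention communities and adverse-event data to the intervention groups, so the Table 4 mark fits. The general statement of identical screening is weak support by itself, since the tables depart from it elsewhere: socio-economic status is at 15 months in Table 3 and at 18 in Table 4.
- *The health care section promises testing throughout.* It says what follows once parasitemia is documented; it does not order a test.

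**Conclusion.** The point holds as an internal contradiction with a practical consequence. Table 4 conflicts with the tests section and the screening section on malaria at 18 months in the delayed group. The size depends on which governs: about 810 children without any post-baseline malaria observation if the table is followed, none lost if the text is. No assumption about prevalence or clustering is needed.

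Separately, and whichever instruction is followed, the analysis section plans a malaria-incidence comparison that the design cannot supply, because the delayed group has no visits between the two screens. The contrasts among the four intervention groups, where the first hypothesis tests malaria, are untouched. So is the growth comparison with the delayed group, since Table 4 marks anthropometry at both 9 and 18 months.

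**What to change.** 1. Mark malaria (parasite count from the 18-month finger stick) at 18 months in Table 4, so that it agrees with the tests, screening and risks sections.
2. In the data entry and analysis section, limit the comparison of all intervention groups with the delayed group to outcomes measured in both kinds of community. Malaria incidence then stays as a comparison among the four intervention groups. Diarrhea incidence, which rests on the same weekly visits, falls under the same limit.
3. If 18-month parasitemia prevalence is reported by group, label it secondary or descriptive, and state that it reflects LNS together with weekly fever testing and treatment in the intervention communities.

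The cost is one table cell and one or two sentences. The visit and the finger stick already take place. Reading the 18-month samples of about 810 children is work that the tests section already plans.
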